### 2.5.2.3 Community controls

Community controls will be children with height/length-for-age Z-score  $\geq -1$ , no wasting and, no chronic disease or disability who are stable resident of the study area and who has no plan to move from the area. They will be recruited from the neighbourhood of children they will be matched with or among children attending the same CBCC. Controls for the body composition sub-study and for the breast-milk intake sub-study, will be

recruited consecutively to the admission of a SAM case into the sub-study. For the post-discharge survival the matching will be done prospectively as children are discharged from the therapeutic feeding phase. The matching ratio will be 1 case for 1 community control for both objectives. The matching criteria will be age ( $\pm 3$  months) and gender.

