Although the information available on the cost-effectiveness of therapeutic feeding centres, and especially community-based management approaches, is sufficient to justify the inclusion of the management of SAM in the child survival strategy, there is still resistance from some policy makers and donors to invest in this intervention over the long term [10, 18, 70-74]. A commonly cited reason behind this resistance is the supposed persistence of a high risk of mortality after recovery from SAM once the patient has exited a treatment programme [75-78]. Data on the longer term mortality associated with discharge from inpatient therapeutic feeding centres is variable; some studies have reported a cumulative mortality rate after 1 to 1.5 years from discharge of up to 41% [75, 76, 79-82], whilst others have reported lower figures of 2.3% after 12 months of follow up, and 4.1% after 1.5 years of follow up [11, 83]. An earlier study reported a mortality of 1.5%, 12 months after discharge among children treated using the domiciliary approach [83]. None of these studies assess the reasons behind the high mortality after discharge from therapeutic feeding programmes, nor do they examine how post-discharge mortality compares with the mortality rate of all children in the same community. Given the strong association between high childhood mortality, poverty and SAM, it may be that baseline mortality rates partly explain both the observed high post discharge mortality and the study- to-study variation. One study that reviewed the existing evidence on long term mortality has shown that children treated in CMAM programmes who start nutrition rehabilitation at an early stage of metabolic malnutrition have long term survival that is comparable to that of children in the same community [84].

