**Other secondary specific objectives:**

- 6 Compare the efficacy of FSMS-RUTF, MSMS-RUTF and P-RUTF in reducing the prevalence of anaemia among children recovering from SAM
- 7 Compare daily intake of RUTF in grams and in kcal/kg/day of children 6 to 59 months treated for SAM with FSMS-RUTF, MSMS-RUTF and P-RUTF (age group 6 to 23 months and 24 to 59 months to be sampled and analysed separately)
- 8 Compare breast milk intake of children 6 to 23 months old treated for SAM with FSMS-RUT, MSMS-RUTF and P-RUTF.
- 9 Compare proportion of children without intestinal inflammation as measured by stools calprotectin at 14 days, 28 days and recovery between SAM children treated with FSMS-RUTF, MSMS-RUTF and P-RUTF.
- 10 Compare recovery in level of plasmatic level of key growth related amino acid of children treated with FSMS-RUTF, MSMS-RUTF, P-RUTF and community controls.
- 11 Compare after discharge survival in SAM children treated with FSMS-RUTF, MSMS-RUTF, P-RUTF and community controls.

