## 2.4 Setting

The research programme will be conducted in the Central Region of Malawi. For the acceptability trial, two CBCCs will be used for the study. We have pre-agreement with several CBCCs but the final choice of the CBCCs will be made in January 2015 based on the functionality and on the number of children attending the centres at that time. The efficacy trial will be carried out in 3 Health District of the Central Region as recommended by the Ministry of Health. These Health Districts are Lilongwe, Dedza and Mchinji. Pre-agreement have been secure with the District Health Officers (DHO) of these Health Districts. In each Health District, a Cluster (a sub-administrative area in Malawi administrative organisation) with the highest burden of acute malnutrition according to the 2014 monthly routine statistics will be selected. In total, 30 community based feeding centres will be established (10 in each District) in the catchment areas of OTP sites that reported more than 60 admissions of SAM cases in 2013. The list will be finalised based on the 2014 statistics and after a field visit has cross-checked the routine statistic figures. The Central region has the worst indicators for undernutrition among under-five children. During the 2010 Malawi Demographic Survey, the prevalence of stunting was 47.2% while that of underweight was 13.5%. The prevalence of wasting is low at 1.8% for severe wasting and 4.3% for wasting. However, this figure underestimates the actual incidence of SAM because up to 80% of cases are oedematous in Malawi and they are not included in these statistics[93]. Indeed, according to

Ministry of Health, by the end of August 25,313 children with SAM had been admitted to CMAM in 2013/2014 consumption year (UNICEF, Malawi situation report, July and August 2014).

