†This CI is inconclusive in that it is still plausible that the true treatment difference is less than  $\Delta$ , but the new treatment is significantly worse than the standard.

From Piaggio et al, JAMA, 2006(295):1152-1160.

For the comparison of survival after discharge from the therapeutic feeding programme, the Kaplan-Meier method will be used to construct survival curves, and the log-rank test and a Cox-regression model will be used

to compare the survival of children who recovered from SAM to that of the community control and assess the effect of some socio-economical and clinical characteristics such as gender, age at discharge, nutrition status at admission and at discharge, HIV status, tuberculosis, and phase angle on survival. Interactions of all the outcomes with the variables gender, form of SAM (oedematous or non-oedematous) and HIV status will be checked.

Given that the study will recruit over a short period of 6 months, no interim analyses will be conducted. However, the independent data monitoring committee will have the right to request Interim analyses if there are reports of several cases of serious side effects.

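### The post-discharge survival controls are chosen by a healthy-reference rule (height-for-age Z of at least -1, no chronic disease), so they do not represent the community the treated children come from

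*Protocol*

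**What the plan says.** Section 2.5.2.3 of the protocol opens with a single definition: "Community controls will be children with height/length-for-age Z-score" of at least -1, and "no wasting and, no chronic disease or disability who are stable resident of the study area". It then describes recruitment for the body-composition and breast-milk sub-studies. For survival it changes only the timing: "For the post-discharge survival the matching will be done prospectively as children are discharged from the therapeutic feeding phase". No separate eligibility rule is given. Matching is on age (within 3 months) and gender, and "The matching ratio will be 1 case for 1 community control for both objectives".

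The survival objective that uses these controls is item 11 of the other secondary objectives in section 2.3.1.2: "Compare after discharge survival in SAM children treated with FSMS-RUTF, MSMS-RUTF, P-RUTF and community controls". Section 2.5.6.2.1 plans Kaplan-Meier curves, a log-rank test and Cox regression "to compare the survival of children who recovered from SAM to that of the community control".

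The literature review (section 2.1) faults earlier studies of post-discharge deaths: "nor do they examine how post-discharge mortality compares with the mortality rate of all children in the same community". It adds that baseline mortality may partly explain the high figures. Section 1.4 likewise takes the general population of the same age and community as its benchmark for long-term survival.

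**The concern.** A well-nourished, healthy child is a sensible reference for body fat, phase angle or breast-milk intake. A survival comparison needs a control that carries the mortality risk of the community the case came from. Requiring good linear growth and no chronic disease removes children who are likely to have higher mortality, and it does so on the control side only. Treated children whose survival exactly matched that of their community could then appear to die more often than the controls.

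Section 2.1 reports that supposed high mortality after discharge is used as a reason not to invest in treatment. A spurious excess in this trial would feed that argument. This is a recruitment rule, so an analysis plan cannot undo it once controls are enrolled.

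**Working it through.** The protocol gives no sample size, event count or power for the comparison with controls, so there is no planned figure to reproduce. Three checks apply.

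**1. Which control filters lack a counterpart among cases?**

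| Control filter (2.5.2.3) | Cases |
|---|---|
| No disability | Disability is an exclusion (2.5.2.2): counterpart |
| Stable resident | Visiting families are excluded (2.5.2.2): counterpart |
| No wasting | Recovered cases have met the arm-circumference and oedema discharge criteria (Table 3): approximate counterpart |
| No chronic disease | HIV and tuberculosis cases are enrolled (2.5.2.2): no counterpart |
| Height-for-age Z of at least -1 | No such criterion, and most SAM children are said to be stunted (1.1): no counterpart |

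The asymmetry lies in the last two rows.

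**2. How selective is the height-for-age filter?**

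The input is section 2.4, which reports for the Central Region that "the prevalence of stunting was 47.2% while that of underweight was 13.5"%. Assumptions: stunting means Z below -2, Z is normal, the SD is 1.0 to 1.5, and the regional figure applies to the study neighbourhoods.

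- The standard normal quantile at 0.472 is about -0.070, so mean = -2 + 0.070 × SD.
- Eligible share = 1 − Φ((−1 − mean) / SD).

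| SD | Mean Z | Share with Z of at least -1 |
|---|---|---|
| 1.0 | -1.930 | 17.6% |
| 1.2 | -1.916 | 22.3% |
| 1.4 | -1.902 | 26.0% |
| 1.5 | -1.895 | 27.5% |

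About 72% to 82% of children are thus excluded before the other filters apply. With no assumption about shape or SD, the 47.2% who are stunted are all excluded.

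**3. Which way does the bias run?**

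Let p be the eligible share and RR the mortality of ineligible relative to eligible children. A cohort dying at exactly the community rate would show a mortality ratio against the controls of p + (1 − p) × RR. The protocol gives no value for RR, so the figures below only illustrate direction.

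| Assumed RR | p = 0.176 | p = 0.275 |
|---|---|---|
| 1.0 | 1.00 | 1.00 |
| 1.25 | 1.21 | 1.18 |
| 1.5 | 1.41 | 1.36 |
| 2.0 | 1.82 | 1.72 |

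Any RR above 1 produces an apparent excess.

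**Can the Cox model repair it?** The listed covariates include HIV status, tuberculosis, and nutrition status at admission and discharge. For HIV and tuberculosis the contrast can be estimated among cases without them, which is a partial answer for a narrower population. Controls have no admission or discharge nutrition status. Stunted cases have no control of similar height-for-age, so adjustment for height-for-age would rest on extrapolation.

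**The case against.** The strongest reply is that the protocol defines its controls openly and promises a comparison with those controls, not with all children. The gap described in section 2.1 is never tied to objective 11. The survival hypothesis itself (item 11 in section 2.3.2.2) compares the three foods within a 10% margin and uses no controls. A healthy reference is a stricter but still interpretable benchmark: survival equal to or better than theirs would be informative. Section 2.1 also cites a review that has already compared treated children with their community.

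Much of this stands. The link from section 2.1 to objective 11 is an inference, although no other objective addresses that gap. The size of the bias is unknown. The analysis also compares children who recovered, and this selection may partly offset the bias. It does not turn the controls into a community sample.

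A reader might infer that every control filter is one-sided, that the comparison is worthless, or that the trial's survival findings are compromised as a whole. The documents do not support any of these. Disability and residence are screened among cases too, and wasting approximately so. A favourable result would remain interpretable, and the comparison between randomised arms does not involve the controls.

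**Conclusion.** The point holds for one non-randomised, secondary comparison: survival of treated children against community controls. The height-for-age and chronic-disease filters apply to controls only. Roughly 18% to 28% of children would meet the height-for-age criterion, given the assumptions in the second check.

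The comparison is probably biased towards apparent excess mortality after treatment. That direction rests on the premise that shorter or chronically ill children have higher mortality, which is plausible but not quantified in the protocol. The amount cannot be estimated from it. As defined, the comparison does not supply the contrast with all children in the community that section 2.1 says is missing. The primary recovery endpoints and the randomised arm-against-arm survival hypothesis are unaffected. The change should be made, but the trial does not depend on it.

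**What to change.** In section 2.5.2.3, keep the present definition for the body-composition, bio-electrical impedance and breast-milk controls. Add a separate one for survival controls:

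- neighbourhood children matched on age (within 3 months) and gender;
- stable residents, without current SAM and without disability, to mirror the case criteria;
- no restriction on height-for-age or chronic disease;
- height, arm circumference and known HIV and tuberculosis status recorded, for description and adjustment.

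The conditions on current SAM and disability are needed. Without them the controls could include untreated cases or children of a kind excluded among cases, which would tilt the comparison the other way.

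If the sponsor prefers the healthy reference, objective 11 and the comparison in section 2.5.6.2.1 should be restated as against well-nourished healthy children, and any interpretation in terms of community mortality dropped.

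The cost is about one sentence, and survival controls become easier to find. The small downside is that one child can serve as both a body-composition and a survival control only if it meets both definitions.

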## 2.5.3 Sample size and randomisation

### 2.5.3.1 Sample size

For the acceptability trial, a convenience sample of 20 children per group will be used. For assessing efficacy, the different sample sizes are calculated for a power of 80% and a level of significance of 0.05. The total sample size will be the total of sample required for the SO1 and SO2. For the other SOs, the calculated sample was lower than that required for the total sample for SO1 and SO2 as indicated in table 2 below.

**Table 2: Sample size according to the specific objective for the efficacy study**

| Specific objective | endpoint                                           | Research design                   | Assumptions                                                                                                      | Calculated sample                               |
|--------------------|----------------------------------------------------|-----------------------------------|------------------------------------------------------------------------------------------------------------------|-------------------------------------------------|
| SO1                | Recovery rate
6-23 months                       | Non-inferiority
clinical trial | Recovery rate
P-RUTF, FSMS-RUTF, MSMS-
RUTF= 75.5%
Non-inferiority margin=10%
Loss to follow up =10% | 250 per arm.
Total=750 SAM children          |
| SO2                | Recovery rate
24-59 months                      | Non-inferiority
clinical trial | Recovery rate P-RUTF, FSMS-RUTF,
MSMS-RUTF = 88.2%
Non-inferiority margin=10%
Loss to follow up =10%    | 150 per arm.
Total=450 SAM children          |
| SO3                | Mean
weight gain
6-23 months                 | Non-inferiority
clinical trial | Standard deviation=4.1
non-inferiority margin =1.5g/kg/d
Loss to follow up=10%                             | 110 children/arm
Total=330 SAM children      |
| SO4                | Mean
weight gain
24-59 months                | Non-inferiority
clinical trial | Standard deviation=3.5
non-inferiority margin =1.5g/kg/d
Loss to follow-up=5%                              | 75 children/arm
Total=225 children           |
| SO5                | Mean
Length of stay
6-23 months              | Non-inferiority
clinical trial | Standard deviation=22.8
non-inferiority margin = 14 days
Loss to follow up=10%                             | 40 children/arm
Total= 120 children          |
| SO6                | Mean
Length of stay
24-59 months             | Non-inferiority
clinical trial | Standard deviation=9.9
non-inferiority margin = 14 days
Loss to follow up=10%                              | 30 children/arm
Total= 90 children           |
| SO7                | Mean
Fat free mass (%)                          | Non-inferiority
clinical trial | Standard deviation=1.62
Margin of non-inferiority = 1.07kg
Loss to follow up=5%                            | 35 per arm
Total=105 children
6-59 months |
| SO8                | Mean
Phase Angle                                | Non-inferiority
clinical trial | Standard deviation=0.7
Margin of non-inferiority = 0.2
Loss to follow up=10%                               | 170/arm
Total= 510 children
6-59 months   |
| SO9                | Mean
height gain
3 months after
discharge | Non-inferiority
clinical trial | Standard deviation=0.7
Margin of non-inferiority = 0.5cm
Loss to follow up=10%                             | 180 /arm
Total=540 children
6-23 months   |
| SO10               | Mean
height gain
3 months after
discharge | Non-inferiority
clinical trial | Standard deviation=0.8
Margin of non-inferiority = 0.3 cm
Loss to follow up=10%                            | 100 /arm
Total=300 children
24-59 months  |
| SO11               | Anaemia rate                                       | Non-inferiority                   | Standard deviation=1.3
Non-inferiority margin = 0.5 g/dl
Loss to follow up=10%                             | 100 /arm Total=300
children (both age group) |

The sample size for non-inferiority assessment is calculated using the software “Power” available at [http://www.sealedenvelope.com/power\\_binary\\_noninferior.php](http://www.sealedenvelope.com/power_binary_noninferior.php) for binary endpoint and [http://www.sealedenvelope.com/power\\_continuous\\_noninferior.php](http://www.sealedenvelope.com/power_continuous_noninferior.php) for continuous endpoint. For binary endpoint, the software uses the formula  $n = f(\alpha, \beta) \times [\pi_s \times (100 - \pi_s) + \pi_e \times (100 - \pi_e)] / (\pi_s - \pi_e - d)^2$  where  $\pi_s$  and  $\pi_e$  are the true percent 'success' in the standard and new (experimental) treatment group respectively  $f(\alpha, \beta) = [\Phi^{-1}(\alpha) + \Phi^{-1}(\beta)]^2$  and  $\Phi^{-1}$  is the cumulative distribution function of a standardised normal deviate [94]. For the continuous endpoint, the Calculation is based on the formula:  $n = f(\alpha, \beta) \times 2 \times \sigma^2 / d^2$  where  $\sigma$  is the standard deviation and  $f(\alpha, \beta) = [\Phi^{-1}(\alpha) + \Phi^{-1}(\beta)]^2$  [95].

### **2.5.3.2 Randomisation**

The study will use simple randomisation and the sealed opaque envelope method will be used for the final allocation of group.

For the acceptability trial, using a pre-established list of sites, eligible children with their caregivers will be invited one by one and asked to pick an envelope containing the study group from a sealed box. No change of envelope will be allowed.

For the efficacy trial, to minimize selection bias and maximize chances of having balanced allocation in all the 3 study groups, a block randomisation with random block size scheme will be used. Thus, in blocks of different sizes (the size will be decided in advance and randomly), children will be prospectively allocated to one of the 2 intervention groups (FSMS-RUTF group or MSMS-RUTF group) or the control group in which the standard RUTF (P-RUTF) will be used. Different randomisation list will be established for 6 to 23 months and 24 to 59 months children.

## **2.5.4 Study implementation approach and procedures**

### **2.5.4.1 Both components: anthropometric procedures**

#### **2.5.4.1.1 Weight**

Weight will be measured at the same time of day at the arrival to the day-care centre. For each site, the weighing will be done by the same team of two persons throughout the study, monitored and supervised closely by the same field research supervisors. All children will be weighed undressed. The weighing will be done following WHO recommended procedures (Training Course on Child Growth Assessment. Geneva, WHO, 2008). For children less than 2 years old or unable to stand, we will do tared weighing. For children 2 years or older, we will weigh the child alone if the child can stand still.

#### **2.5.4.1.2 Height/Length**

The height/length will be done following WHO recommended procedures (Training Course on Child Growth Assessment. Geneva, WHO, 2008). A locally made wood height/length board will be used for the measurement. Depending on a child's age and ability to stand, we will measure the child's length (length is measured lying down) or height (height is measured standing upright). Children will be measured with height board placed on a flat, stable surface such as a table for length or against a straight, vertical surface such as a wall or pillar for height with the head, back, buttocks, and heels touching the backboard; heels together; knees extended; and head in the Frankfort horizontal plane. The measurement will always be done by two researcher officers. One person will be considered as principal measurer and the second as his assistant.

#### **2.5.4.1.3 MUAC**

MUAC will be measured using a standard MUAC tape. The measurer will locate the tip of the child's shoulder and bent the elbow to the right angle, mark the midpoint of the arm by measuring from the tip of the shoulder

and tip of the elbow, straighten the child's arm and wrap the tape around the arm at the mid-point, make sure the numbers on the tape are right side up and tension is not too tight and too loose.

#### 2.5.4.2 Acceptability trial

##### 2.5.4.2.1 Intake monitoring

The Intake during both phases will be monitored by the research team. Children will attend the feeding point according to the usual opening hours of CBCCs. During the stay at the feeding point of the CBCC, children will be offering a 92g sachet of RUTF that they should consume in 3 servings. They will be offered the possibility to ask for more if they finish their sachet. Each meal intake will be recorded and the specific information collected will include:

- quantity given
- quantity eaten
- quantity of waste or spillover
- eating pattern (food refusal, need for support and insistence to eat, duration of the meal)
- request of additional amount

